### MasterChef Analysis

MasterChef will be evaluated initially for feasibility through a qualitative focus group design along with an expert content analysis. After modifications to the program based on feasibility analysis, the intervention will be evaluated using a matched-based cohort design with the non-MasterChef control group selected based on gender, ethnicity, and year in college matched-based design, with a focus on gender, ethnicity, and year in college. Descriptive and frequency statistics were used to analyze the sample’s baseline and demographic data. A 2-way repeated-measures analysis will be used to assess significant changes in baseline and postintervention outcomes within the experimental group and as a comparison with the control. Participants will complete the aforementioned nutrition measures before the week-long Fall 2023 program delivery, directly after the program, and again at the end of the semester. A control will be recruited through a matched-based design. A 2-way repeated-measures ANOVA will be used to identify significant changes between baseline data, postintervention data, and follow-up data between the intervention and control group. The program will also be implemented in the format of monthly workshops. A multivariate ANOVA will be used to compare health outcomes between curriculum formats. Multiple linear regressions will be used to identify predictors of diet quality using the combined fall and spring samples. Significance levels will be set at *P*<.05.

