### Measures

#### Comprehensive Wellness Survey

After completing a web-based consent form, participants complete a comprehensive health behavior survey. This survey is distributed during week 4 and again during week 14 (the week before finals week) in the fall and spring semesters. Week 4 was selected based on the typical nursing student’s academic loads and stress. Examinations and competency testing begin each semester’s third to fourth week, accelerating stress during those periods. Participants complete the comprehensive health behavior survey during designated class or work time. Additional measures are collected before specific engagement in targeted study interventions. Participants’ answers are tracked through the project using unique ID codes. As listed below, several variables are assessed to capture the health of nursing students. The comprehensive measurement strategy aligns with Priority Area 2 from the National Academy of Sciences [8], which recommends the longitudinal use of valid and reliable measurements of burnout and factors that mitigate burnout to drive effective interventions and data-driven decision-making at the organizational level.

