#### Nutrition

Nursing students report poor diet quality and dietary behaviors elicited by high levels of perceived stress, peer influence, and academic workload [62]. The impact of mindful eating may mediate this relationship [63]. Mindful eating describes applying mindfulness practices to internal hunger and satiety cues and incorporating a nonjudgmental, self-compassion–led viewpoint in navigating dietary choices [64]. Mindful eating interventions effectively improve several health behaviors, including reducing extreme dieting behaviors, improving portion control, and weight reduction within some populations [65,66]. This study aims to examine the effect of the newly developed program, MasterChef Nursing Edition, on nursing students’ diet quality, resilience, burnout, and well-being.

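### MasterChef aims to affect burnout and resilience, but its three assessments carry only nutrition measures, and the common survey can fill at most two of the three occasions

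*Protocol article*

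**What the plan says.** The Nutrition section (under Discussion) lists four outcomes for MasterChef: "diet quality, resilience, burnout, and well-being".

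The MasterChef Analysis section fixes content and timing in one sentence, whose final occasion is the close of the semester: "Participants will complete the aforementioned nutrition measures before the week-long Fall 2023 program delivery, directly after the program, and again at the end of the" ...

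The measures described under Nutrition Assessments are the Mindful Eating Questionnaire, the food preparation survey, the Body Appreciation Scale, weight satisfaction and the Short Healthy Eating Index.

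The same section describes the analysis twice. The first description has two occasions: "A 2-way repeated-measures analysis will be used to assess significant changes in baseline and postintervention outcomes within the experimental group", and also against control. The second is a 2-way repeated-measures ANOVA on three, to identify "significant changes between baseline data, postintervention data, and follow-up data between the intervention and control group".

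The Oldenburg Burnout Inventory (16 items) and the Brief Resilience Scale (6 items) belong to the Comprehensive Wellness Survey: "This survey is distributed during week 4 and again during week 14 (the week before finals week) in the fall and spring semesters".

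**The concern.** The aim, the instruments, the occasions and the model are all stated in the article, and for burnout and resilience they do not fit together. Followed as written, no burnout or resilience score is tied to the week-long program, and nothing secures one directly after it.

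This matters because lowering burnout and raising resilience is the overarching purpose under WellNurse Project Goals. The Discussion also says that interventions shown to work on such outcomes will go into the standard curriculum. MasterChef could be judged on poorly timed burnout data, or on none. An analysis plan written later can choose a model, but it cannot recover scores that were never collected.

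**Working it through.** No sample size, power or alpha figure is at issue. The check compares the occasions that the analysis needs with the occasions on which each outcome is measured.

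**Inputs**
- Occasions in the second ANOVA description: 3 (MasterChef Analysis).
- Burnout or resilience scales among the nutrition measures: 0 (Nutrition Assessments).
- Common surveys per semester that contain both scales: 2, at weeks 4 and 14 (Comprehensive Wellness Survey).
- Week of the Fall 2023 program: not given.
- Source of controls: recruited by matching. The section does not say that they come from the WellNurse pool or take the common survey.

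**Occasions filled for burnout and resilience, by program week**

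| Program runs | Before | Directly after | End of semester | Filled |
|---|---|---|---|---|
| Between weeks 4 and 14 | week 4 | none, unless the program ends at the week-14 survey | week 14, roughly | 2 of 3 |
| Before week 4 | none in the same semester | week 4 only if the program ends next to it | week 14, roughly | 1 or 2 of 3 |
| In week 4 | week 4 if the survey comes first | week 4 if the survey comes second | week 14, roughly | 2 of 3 |

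A program at about week 14 gains nothing: the week-14 survey then serves one occasion, and week 4 is the only other score. In every case the count is at most 2, because two surveys cannot fill three occasions. Where week 4 does serve as baseline, the directly-after value is the one missing, or it can be had only by giving up a separate follow-up.

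**Interval.** In the favourable case the change runs from week 4 to week 14, which is 14 − 4 = 10 weeks around a 1-week program. The second survey falls one week ahead of finals.

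**Controls.** A two-occasion group-by-time comparison needs both surveys from the controls too. The MBSR Analysis section provides for this: controls come from the WellNurse pool and are assessed at the same intervals as participants, immediately before the first session and after the last. The MasterChef section has no such statement for burnout or resilience.

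**Items to add.** 16 (burnout) + 6 (resilience) = 22. With the 5-item Satisfaction with Life Scale, 22 + 5 = 27. Over three occasions that is 22 × 3 = 66 or 27 × 3 = 81 item responses per person.

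**The case against.** The strongest reply is that the Abstract describes intervention-specific measures as additional, so MasterChef participants still take the common survey, and listing only nutrition measures is consistent with that structure. This stands. A reader might infer that no effect on burnout or resilience can be estimated at all, and the article does not support that. If the program falls between the surveys and controls complete both, a two-occasion comparison is possible, and the first description of the analysis asks for no more.

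Other points also stand:
- The section never says that the three-occasion ANOVA covers burnout or resilience. It follows the sentence on nutrition measures and fits them.
- A reader might infer that the only baseline burnout score follows exposure. That could apply to new enrollees if the program ran before or in week 4. Data collection began in March 2022 and answers are linked by ID code, so continuing participants may have scores from an earlier semester.
- A reader might count well-being as a third unmeasured outcome. The article does not tie that word to the Satisfaction with Life Scale, and body appreciation or weight satisfaction may cover part of it. Only burnout and resilience are clearly absent.
- The 10-week interval concerns the week-long format. Surveys at weeks 4 and 14 suit the monthly workshops better.

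The last reply is that a condensed article may leave the mapping of outcomes to occasions to the registered protocol. That would excuse silence. Here the article does state the aim, the measures and the occasions, and it leaves burnout and resilience out of the last two.

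**Conclusion.** The point holds for burnout and resilience. The MasterChef schedule provides 0 of 3 occasions for them, and the common survey provides at most 2 of 3, with no secured value directly after the program. On the stated schedule the three-occasion ANOVA cannot be run for these two outcomes. A two-occasion controlled comparison is possible but not assured, since it depends on the program week and on controls taking the survey, and the article settles neither.

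This rests on two assumptions: that the nutrition measures are those listed under Nutrition Assessments, and that no fuller document adds the two scales to the MasterChef surveys. It is a gap worth closing because closing it is cheap. It does not affect the nutrition outcomes, for which the three-occasion plan is coherent.

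**What to change.** Preferred: add the Oldenburg Burnout Inventory and the Brief Resilience Scale to the MasterChef surveys at all three occasions, for participants and matched controls. Add the Satisfaction with Life Scale if that is the intended well-being measure, and say so. The project already uses all three scales in its common survey. The cost is 22 items (27 with life satisfaction), a few more minutes per survey for participants and controls.

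If that burden is refused: hold the week-long program between the week-4 and week-14 surveys, draw controls from participants who complete both, and analyse week-14 burnout and resilience adjusted for week 4. State that no immediate effect on these outcomes is estimable. This adds no items, but it constrains the calendar, narrows the pool of controls and gives up the immediate effect.

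Either way, the MasterChef Analysis section should say which occasions, which controls and which of its two described analyses apply to burnout and resilience.

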## Results

### Overview

The project was funded on January 1, 2022. Data collection started in March 2022. A total of 267 participants have been recruited. Results will be published after each semester starting in December 2023.

The primary study variables will be analyzed 4 times per year to track population outcomes and changes. Regression analysis will be conducted to examine the relationship of students’ on-time progression, stress, resilience, and burnout with physical and emotional health variables and on-time progression. Subanalysis will be conducted for unique groups such as first and fourth year students, faculty and staff, and graduate students, as well as students from historically underrepresented populations such as first-generation college students and racial and ethnic minorities. Additionally, program retention, on-time graduation, and faculty and staff retention will be tracked over time. The cost of implementing MBSR, massage therapy, MasterChef, and fitness events will be tracked to determine cost per student. Additionally, feasibility will be measured using qualitative focus group interviews with students who complete specific interventions along with attrition rates for completing specific interventions such as MBSR and MasterChef.

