### MBSR Analysis

Quantitative evaluation of MBSR outcomes will be conducted by comparing MBSR participants with matched control participants at selected intervals with regard to key study variables (eg, stress, burnout, and mindfulness skills). Participants enrolled in MBSR are assessed immediately before their first MBSR session and immediately after completing the final MBSR session. Matched controls are identified for each MBSR participant by randomly selecting nonenrolled individuals from the WellNurse participant pool on the basis of identical gender identity, birth year, and role (faculty, staff, and student). Controls are assessed at the same intervals as MBSR participants.

Statistical analysis will test whether MBSR participants differ significantly from controls with regard to postintervention levels of each outcome variable, controlling for preintervention levels. ANOVA models will be used to conduct initial comparisons. With time, larger samples, and thus more statistical power and more complex models (eg, multilevel modeling), can be tested to evaluate the potential impact of instructor, delivery modality (in-person vs remote), duration (1 week vs 8 weeks), and dose (number of sessions attended), as well as individual participant characteristics (eg, gender identity and role). Ongoing assessments for all WellNurse participants will allow for longer term follow-up of MBSR and control participants with regard to distal outcomes of interest (eg, academic retention). We expect significant differences between MBSR and control participants; immediate postintervention effects may be strongest, with somewhat weaker longitudinal effects observed over time. Analyses will also be able to test whether those participants who engage in ongoing mindfulness practice after formal MBSR training may experience improved outcomes as compared with those individuals who discontinue regular practice.

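### MasterChef's three-survey comparison is tied to a repeated-measures ANOVA that, as usually run, uses only complete cases and omits the matching factors; a mixed model on all available surveys suits the design better

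*Protocol article*

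**What the plan says.** All of this is in the protocol article, under Results.

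- **Test.** The MasterChef Analysis section names the method: "A 2-way repeated-measures ANOVA will be used to identify significant changes between baseline data, postintervention data, and follow-up data", compared between the intervention and control groups. "Significance levels will be set at" P<.05.
- **Occasions.** The nutrition measures are taken "before the week-long Fall 2023 program delivery, directly after the program, and again at the end of the semester".
- **Controls.** The design is a "matched-based cohort design with the non-MasterChef control group selected based on gender, ethnicity, and year in college". The section later repeats: "A control will be recruited through a matched-based design". It gives no matching ratio and does not say whether controls are matched one to one or as a group. No term for the matching is named in the analysis.
- **A second description.** Before the three-occasion ANOVA, the same section describes a two-way repeated-measures analysis of baseline and postintervention outcomes, within the experimental group and against the control. It does not say whether this is a separate two-occasion analysis or a looser statement of the same one.
- **Attrition and numbers.** The Overview lists "attrition rates for completing specific interventions such as MBSR and MasterChef" as a feasibility measure. It also says "A total of 267 participants have been recruited", which is the whole WellNurse project. No MasterChef sample size, effect size, SD or survey response rate is given.
- **Other models.** The MBSR Analysis section says that, with larger samples, "more complex models (eg, multilevel modeling), can be tested". No such option is mentioned for MasterChef.

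**The concern.** This is about a method the article names. It is not a complaint that a missing-data policy is absent. A conventional repeated-measures ANOVA has three properties that fit this design poorly.

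1. It needs every score from each person. Someone with one missing survey adds nothing to the three-occasion comparison, although their other two surveys are informative.
2. It assumes sphericity. That is doubtful when the first two surveys lie about a week apart and the third comes at the end of the semester.
3. The two factors are group and occasion, so gender, ethnicity and year in college, on which the controls are selected, do not enter the model.

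At stake are precision in what may be a small comparison and, under one particular dropout pattern, a biased group contrast. That pattern is conceivable here because the groups are not randomised and students in designated courses receive credit for attending, so reasons for staying may differ between groups.

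**Working it through.** The article has no MasterChef figure to reproduce. Every rate and correlation below is an assumption, chosen to show the range.

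**1. Complete cases and the baseline-to-post standard error.** Let m be the proportion missing at each of the two later surveys, independently.

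- Share with all three surveys: (1 − m)².
- Share with baseline and post: 1 − m.
- Standard error ratio, complete cases to all available pairs: √[(1 − m)/(1 − m)²] = 1/√(1 − m).

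| m | all three surveys | baseline and post | SE ratio |
|---|---|---|---|
| 0.10 | 0.81 | 0.90 | 1.054 |
| 0.20 | 0.64 | 0.80 | 1.118 |
| 0.30 | 0.49 | 0.70 | 1.195 |

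The inflation is therefore about 5% to 20%. If the same people miss both later surveys, the two shares are equal and the ratio is 1.

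**2. Precision for the end-of-semester contrast.** Here a mixed model recovers less, because the missing score is the one being compared. In a simulation with 50 per group, 10% to 30% missing the third survey only and unrelated to scores, and correlations of 0.6 (baseline–post), 0.6 (post–follow-up) and 0.5 (baseline–follow-up), the SD of the estimated effect was:

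| missing | complete cases | likelihood, all surveys | reduction |
|---|---|---|---|
| 10% | 0.214 | 0.210 | 2% |
| 20% | 0.220 | 0.213 | 3% |
| 30% | 0.237 | 0.224 | 5% |

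**3. Bias.** Assume no true effect, a baseline–post correlation of 0.6, and third-survey response that depends on the post score in one group only. Among completers in that group, the change from baseline is shifted by (1 − 0.6) × E[post score | survey 3 completed], in SD units. The other group is not shifted, so this is the bias in the contrast.

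| missing at survey 3 in that group | log odds 0.5 per SD | log odds 1.0 per SD |
|---|---|---|
| 10% | 0.020 | 0.036 |
| 20% | 0.038 | 0.069 |
| 30% | 0.057 | 0.101 |

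The range is 0.02 to 0.10 SD. With all baseline–post pairs the bias in this contrast is zero, because nobody is removed from it.

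A separate simulation used 200,000 per group, a true effect of 0.40 SD, correlations 0.6, 0.7 and 0.5, log odds 1.0 per SD and base dropout of 10% to 30%:

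- Dropout depending on the baseline or post score in one group only: complete-case estimates of the two contrasts ran from 0.265 to 0.512, while the likelihood estimates stayed at about 0.40.
- Dropout unrelated to scores, or related equally in both groups: both methods gave about 0.40.

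**4. Matching.** If controls are individually matched with within-pair correlation r, the paired-to-unpaired standard error ratio is √(1 − r). The true two-sided level of a nominal 0.05 test that ignores the pairs is 2[1 − Φ(1.96/√(1 − r))].

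| r | SE ratio | true level |
|---|---|---|
| 0 | 1.00 | 0.050 |
| 0.1 | 0.95 | 0.039 |
| 0.2 | 0.89 | 0.028 |
| 0.3 | 0.84 | 0.019 |

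Ignoring positive pairing makes the test conservative. The point estimate is unchanged.

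**The case against.** The strongest reply is that the article never says incomplete participants are dropped. A repeated-measures ANOVA can be run on imputed data, and the handling of missing surveys is commonly left to an analysis plan that is not shown. This stands: listwise deletion is how the named method is usually run, not something the article states. It does not remove the point. A plan that follows the named test inherits its properties unless something is added, and a plan that uses a mixed model would depart from the published wording.

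A reader might infer that a student who misses the end-of-semester survey is lost even from the before-after comparison. The article does not support that. Its separate sentence on baseline and postintervention outcomes may describe an analysis that needs only two surveys, in which case that student stays in it. The standard error figures in step 1 and the bias table in step 3 therefore apply only to the baseline-to-post contrast taken from the three-occasion model.

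A reader might also infer that each control is paired with a participant and that the pairing is wrongly ignored. The MasterChef text describes a control group selected on three factors, which fits group matching equally well. Individual matching is explicit only for MBSR. If pairs do exist, ignoring them costs precision and does not bias the result.

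Three further objections stand:

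- The attrition the Overview plans to track concerns completing the program, not answering surveys, so it supplies no non-response rate.
- Unequal spacing is not a fault in itself, since the ANOVA treats occasion as categorical, and standard corrections for non-sphericity exist.
- A mixed model with only a participant random intercept would keep the equal-correlation assumption, so the covariance structure has to be specified.

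**Conclusion.** The point holds in a limited, conditional form. The named ANOVA is a recognised method and nothing in the article is contradictory or miscalculated, but it is a weaker choice for three surveys with a matched control group than a readily available alternative.

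The loss is modest and rests wholly on assumed dropout. It is about 5% to 20% in the baseline-to-post standard error within the three-occasion model at 10% to 30% independent missingness, and none if the same people miss both later surveys. The gain for the end-of-semester contrast is about 2% to 5%. Bias, roughly 0.02 to 0.10 SD for the baseline-to-post contrast under the post-score mechanism in step 3, requires dropout that depends on scores differently in the two groups; without that difference there is none. The wider range in the second simulation is specific to its own assumptions, which include dropout driven by the baseline score. The matching part concerns precision only.

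**What to change.** In the MasterChef Analysis section and the analysis plan, replace the three-occasion ANOVA with a linear mixed model for repeated measures fitted to all available surveys. Include:

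- group, occasion (three levels) and group × occasion;
- gender, ethnicity and year in college as covariates;
- an unstructured within-participant covariance, not a random intercept alone;
- a matched-set effect only if controls are individually matched, with the type of matching stated.

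Draw the conclusions from the group × occasion contrasts at postintervention and at end of semester. These cover the baseline-to-post comparison too, so also say whether the sentence on that comparison is a separate analysis or part of this model.

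The model is unbiased for dropout that depends on observed scores; it does not protect against dropout that depends on unobserved ones. The cost is revised wording and a small amount of analysis work. No new data are needed, and with complete data and sphericity the group-by-occasion test is essentially that of the ANOVA, so little is given up.

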### MasterChef: Nursing Edition

This monthly workshop is innovative in combining gamified learning, cooking self-efficacy, mindful eating, and nutrition education for prelicensed nursing students. The course outline consists of (1) mindful eating concepts, (2) nutrition education, (3) participants designing their own healthful and accessible recipe, (4) participants mindfully eating and voting on their favorite meal, and (5) discussion and application to clinical practice. Participants are also encouraged to do 2 “homework” assignments per week, each emphasizing healthy eating or mindfulness behaviors. Participants also receive ingredients for recreating their healthful recipe at home and a “dorm-friendly” recipe book developed by a registered dietitian nutritionist. All students, staff, and faculty are encouraged to join, but students in designated courses receive credit for attendance.

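### The MasterChef format MANOVA and control ANOVA name no workshop-group term, so the format test can exceed its 5% level by an amount that depends on unstated ICC and group size

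*Protocol article*

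**What the plan says.** The section MasterChef: Nursing Edition describes a shared activity. Its outline includes "participants mindfully eating and voting on their favorite meal", followed by a discussion. Anyone in the school may join, and "students in designated courses receive credit for attendance".

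The section MasterChef Analysis then names three analyses:

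- **Against matched controls:** "A 2-way repeated-measures ANOVA will be used to identify significant changes between baseline data, postintervention data, and follow-up data". Measurements are taken "before the week-long Fall 2023 program delivery, directly after the program, and again at the end of the semester". Controls are matched on gender, ethnicity and year in college.
- **Week-long versus monthly format:** "A multivariate ANOVA will be used to compare health outcomes between curriculum formats".
- **Predictors of diet quality:** "Multiple linear regressions will be used to identify predictors of diet quality using the combined fall and spring samples".

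The section closes with "Significance levels will be set at" P<.05. It mentions no effect for workshop group, session or course. Multilevel modelling appears only in MBSR Analysis, as a later option for studying instructor, modality, duration and dose. The number of MasterChef groups, their size and any ICC are not given.

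**The concern.** The repeated-measures ANOVA allows for correlation within a person over time, and the MANOVA for correlation between outcomes. Neither allows for people in the same workshop group responding alike. Shared food, a shared vote, a shared discussion and one session leader are all plausible sources of such likeness. If it exists, the standard errors are too small, and a good or poor group can be read as an effect of format or program.

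The Discussion (Principal Findings) says that interventions shown to work will be built into the standard nursing curriculum. The control comparison bears on that decision most directly. A false positive in the format comparison would mainly favour one delivery of the same program over the other.

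**Working it through.** **Inputs.** From the article: alpha 0.05; both formats delivered in groups; controls selected individually. Assumed, because the article does not give them: ICC 0.01 to 0.10, group size m from 6 to 20, equal arms, and (for matching) a within-pair correlation r.

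**Step 1: the plan's own figure.** The actual level of a test that ignores a variance inflation DE is 2 × (1 − Φ(1.96/√DE)). With independent participants DE = 1 and the level is 0.050, as stated.

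**Step 2: format comparison, one outcome.** Both arms are grouped, so DE = 1 + (m − 1) × ICC. Example: m = 10, ICC 0.05 gives DE = 1 + 9 × 0.05 = 1.45 and a level of 0.104.

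**Step 3: control comparison.** Only the MasterChef arm is grouped, so DE = 1 + (m − 1) × ICC/2. Example: m = 10, ICC 0.05 gives DE = 1.225 and a level of 0.077. The relevant ICC here is that of change over time.

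| m | ICC | Format, one outcome | Control comparison |
|---|---|---|---|
| 6 | 0.01 | 0.056 | 0.053 |
| 10 | 0.01 | 0.060 | 0.055 |
| 10 | 0.02 | 0.071 | 0.060 |
| 10 | 0.05 | 0.104 | 0.077 |
| 10 | 0.10 | 0.155 | 0.104 |
| 20 | 0.01 | 0.072 | 0.061 |
| 20 | 0.05 | 0.160 | 0.107 |
| 20 | 0.10 | 0.250 | 0.160 |

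Simulation (6,000 runs per cell) agrees: for 4 groups of 10 per arm at ICC 0.05 it gave 0.102 and 0.076.

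**Step 4: format MANOVA.** Simulated as Hotelling's T² on 5 mutually independent outcomes, 6,000 runs per cell. With 4 groups of 10 per format the level was 0.051 at ICC 0, then 0.076, 0.093, 0.176 and 0.317 at ICC 0.01, 0.02, 0.05 and 0.10. Over m = 6 to 20 it ran from 0.059 (6 groups of 6, ICC 0.01) to 0.57 (2 groups of 20, ICC 0.10). The excess is larger than for one outcome because group shifts accumulate across outcomes.

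**Step 5: offset from matching.** If matched pairs correlate by r in their change and the ANOVA ignores the pairing, DE = (1 − r) + (m − 1) × ICC/2. With m = 10 and ICC 0.02:

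- r = 0.1: DE = 0.90 + 0.09 = 0.99, level 0.049
- r = 0.2: DE = 0.80 + 0.09 = 0.89, level 0.038

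**Step 6: repeat attendees in the combined regression.** If a fraction p of people contribute two rows correlated 0.5, inflation for a person-level predictor is (1 + 2p)/(1 + p).

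- p = 0.1: 1.2/1.1 = 1.09, level about 6%
- p = 0.2: 1.4/1.2 = 1.17, level about 7%

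**The case against.** **This is a condensed article.** Random effects are often left to a fuller plan. That limits the point to what is printed. But the section does name its tests, and those tests assume independent participants. MBSR is given a multilevel option and MasterChef is not.

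**The size is unknown.** This stands. A reader might infer that both tests run well above 5%. The article does not support that: at ICC 0.01 with groups of 10, the one-outcome format test is at 0.060 and the control comparison at 0.055.

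**The control comparison is protected in part.** This also stands. Only one arm is grouped, stable differences present at baseline largely cancel in the group-by-time test, and unmodelled matching works the other way.

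**Repeat attendance.** A reader might infer that people who attend both formats inflate the MANOVA. The direction is the opposite: the same person in both arms creates positive covariance between them, which makes an independent-samples test conservative. For the combined regression, a level of about 11% follows only if everyone contributes two rows. The article says nothing of the kind, nor does it say that repeat rows would be treated as different people.

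**Courses as clusters.** It is tempting to say participants are drawn through designated courses. The workshop is open to all, and those courses only give credit.

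**A group effect may be hard to fit.** This stands. Few groups give a poor estimate of group variance. The article does not say whether monthly groups are fixed; if people move between sessions, groups are crossed rather than nested.

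**Conclusion.** The point holds in a limited form. The two MasterChef comparisons are specified without a workshop-group effect although delivery is in groups. The format comparison then exceeds 5% under any positive within-group correlation. Under the assumed ICCs and group sizes the level is about 6% to 25% for one outcome, and about 6% to 57% for a 5-outcome MANOVA. The control comparison ranges over about 5% to 16% before any matching offset, and may sit at or below 5% after it. These are illustrations, since neither ICC nor group size is stated; with an ICC of zero both tests hold their level.

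One part does not depend on the ICC value. The article refers to the week-long Fall 2023 delivery in the singular and does not say how many groups it comprises. If it is one group, format and group coincide and no model can separate them.

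**What to change.** In MasterChef Analysis:

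1. Replace the MANOVA and the 2-way repeated-measures ANOVA with linear mixed models that have a person effect and a workshop-group effect. Define the group as the session or delivery group attended, taken from the sign-in records (Attendance Records). If attendees move between monthly sessions, specify the group effect as crossed.
2. For the control comparison, place the group effect in the MasterChef arm only.
3. Use small-sample degrees of freedom (Satterthwaite or Kenward-Roger).
4. If the week-long format is a single group, or there are too few groups to estimate group variance, report the format contrast as descriptive without a P value.
5. In the combined fall and spring regression, use one record per person or a person random effect, linked by the existing ID codes (Comprehensive Wellness Survey).

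The cost is mainly analysis wording, plus a check that sign-in identifies the session. Intervals will be wider and degrees of freedom few, substantially so if groups are few. As a rough guide, the format contrast has about the number of groups minus two: 4 groups per format leaves 8 − 2 = 6, and 2 per format leaves 4 − 2 = 2.
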